### Aim

The main objective of the RCT is to investigate the effectiveness of HL in terms of a reduction of depressive symptoms in pre-vocational students aged 12 to 14 after 6 months compared to care as usual. We hypothesize that adolescents who participate in the HL-program will have lower levels of depressive symptoms at 6-months follow-up than adolescents who do not participate. Secondary outcomes that will be investigated are well-being and life satisfaction. We hypothesize that students who receive HL report higher levels of well-being and life satisfaction than students who do not receive HL.

In addition, we want to identify potential mediator factors that increase or decrease the intervention’s effectiveness. We will investigate school and class climate indicators. We hypothesize that students who receive HL will report higher levels of classmate support, teacher support, and school connectedness, and lower levels of bullying, which will lead to a reduction of depressive symptoms among students.

A secondary aim of this study is to evaluate the implementation process of the HL-program, from the perspectives of intervention recipients, implementers, and the broader stakeholders at the school level (e.g. teachers). The aim of this evaluation will be to understand how the intervention was implemented and what factors might be important when sustaining or expanding the HL-program over time or in new schools.

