### Design of the RCT

The effectiveness of HL will be tested within a cluster RCT with two conditions: an intervention condition (receiving HL during the study) and a control condition (care as usual, HL will be delivered after the final follow-up assessment). Participating classes will be randomly assigned to either the intervention or the control condition and will be equally distributed across the two conditions within each schoolyear. This design is chosen to avoid a skewed distribution of participants over the two conditions due to school effects. The randomization will be conducted by an independent statistician. Three assessments will be performed in the study: T0 (pre-test, before the start of HL in intervention group); T1 (3-months follow up); T2 (6-months follow-up).

Data will be collected in two cohorts: the first cohort is planned in the 2021-2022 school year and the second cohort is planned in 2022-2023 school year.

See Fig. 2 for the flowchart of the study and Table 1 for an overview of the schedule of enrolment, interventions, and assessment.

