Mediation analyses will be performed to examine potential working mechanisms of the effect of the intervention. Research has shown that there is an association between school climate and mental health of students [50]. Positive relationships between students and their teachers or peers increased psychosocial well-being [50]. Moreover, teacher support reduced depressive symptoms [51]. In addition, higher school connectedness (attachment and belonging to school) was positively associated with students’ psychosocial well-being [50] and acted as a buffer against depressive symptoms and anxiety [51, 52]. Finally, causal associations were found between bullying and depression [53]. Therefore, the following variables will be tested as potential mediators: classmate support, teacher support, school connectedness, and bullying. The categorical variable condition will be included as independent variable in all mediation models (0 = control, 1 = intervention), and the observed scores of primary or secondary outcomes at follow-up as dependent variable. Total, direct, and (total) indirect effects with 95% bootstrapped confidence intervals will be calculated for all mediation models [54, 55].

Furthermore, exploratory moderator analyses will be conducted to examine whether the effect of the intervention on primary and secondary outcomes depends on a priori defined variables. Various sociodemographic factors have an influence on interventions focused on depressive symptoms or well-being. Research has shown that girls might experience more benefits from depression prevention programs than boys [56]. Moreover, older participants might benefit more from cognitive-behavioral therapy [24, 57]. In addition, research has shown that depression prevention programs are likely to be more effective for adolescents with ethnic minority backgrounds [24], since they report more problems with mental health compared to adolescents with ethnic majority backgrounds [32]. Therefore, the following variables will be examined as potential moderators: level of baseline CES-D depressive symptoms, gender, age, and immigration background. Separate linear mixed models with condition, the putative moderator, and the interaction of these two as fixed effects will be used to examine potential moderation effects.

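### The mediation models do not carry over the class clustering and baseline scores of the main models and name no waves, although classes are randomised and a causal chain is hypothesised

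*Protocol article*

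**What the plan says.** The mediation paragraph of the Protocol article (Statistical analyses) fixes four things.

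- Exposure: "The categorical variable condition will be included as independent variable in all mediation models (0 = control, 1 = intervention").
- Mediators: "the following variables will be tested as potential mediators: classmate support, teacher support, school connectedness, and bullying".
- Outcome: "the observed scores of primary or secondary outcomes at follow-up as dependent variable".
- Inference: "Total, direct, and (total) indirect effects with 95% bootstrapped confidence intervals will be calculated for all mediation models".

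It mentions no class effect, no baseline mediator or outcome, no resampling unit, and no wave for mediator or outcome.

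The hypothesis is directional. The Aim section expects "higher levels of classmate support, teacher support, and school connectedness, and lower levels of bullying, which will lead to a reduction of depressive symptoms". On allocation, Design of the RCT says "Participating classes will be randomly assigned to either the intervention or the control condition". The same section sets three assessments: T0 before the programme, T1 at 3 months and T2 at 6 months.

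**The concern.** Three features of the trial make the omissions matter.

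**Clustering.** The class is the randomised unit, and students in one class rate largely the same classmates and teachers. Between-class variance is therefore plausible in the mediators, and it enters the condition-to-mediator path directly. A bootstrap that resamples students as independent would give indirect-effect intervals that are too narrow.

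**Baseline.** Randomisation protects the effect of condition on the mediator. It does not protect the path from mediator to outcome. Climate and mood are both reported by the same student, so stable differences between students (a low-mood student also feels less supported) would pass as mediation unless baseline values are held fixed.

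**Time order.** If mediator and outcome come from the same wave, symptoms may be driving the climate ratings. With two follow-up waves, three pairings have the mediator no later than the outcome (T1 with T1, T1 with T2, T2 with T2), and the text does not choose among them.

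At stake is the claim about why the programme works, which the Discussion lists among the secondary aims and the study's strengths.

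**Working it through.** **Side by side.** Within Statistical analyses, the main models are linear mixed models with students nested in classes and with baseline scores entered. The post-hoc ANCOVA also includes baseline scores. The moderator analyses are again linear mixed models. Mediation is the one inferential analysis described with neither a clustered model nor baseline scores.

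The climate scales are listed under Secondary outcomes, so the mixed models may cover the effect of condition on climate. They would not cover the indirect effect or its interval.

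**Size if clustering is ignored.** The plan states no figure for the mediation analysis, so there is none to reproduce. Inputs:

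- Class size 22 and 40% non-consent (Sample size): 22 × 0.60 = 13.2 participating students per class, if non-consent is spread evenly.
- Cluster size variation 0.17 (Sample size), read as a coefficient of variation.
- ICC of the mediators: not given, so assumed over 0.02 to 0.20. For orientation, the plan uses 0.02 for the outcome and cites 0.01 to 0.07 for depressive mood.

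Formulas:

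- Design effect DE = 1 + ((1 + 0.17²) × 13.2 − 1) × ICC = 1 + (1.0289 × 13.2 − 1) × ICC = 1 + 12.581 × ICC.
- False-positive rate of the condition-to-mediator path at nominal 5% = 2 × (1 − Φ(1.96/√DE)).

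Example, ICC 0.05: DE = 1 + 12.581 × 0.05 = 1.629; 1.96/√1.629 = 1.536; rate = 12.5%.

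The last two columns come from a simulation of the indirect effect itself: 48 classes of 13, no true condition-to-mediator effect, mediator-outcome slope −0.3, outcome class ICC about 0.02, percentile bootstrap with 400 resamples, 400 runs. Simulation error is about 1 to 2 points.

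| Mediator ICC (assumed) | DE | Path false-positive rate | Coverage of 95% interval for the path | Indirect effect, students resampled | Indirect effect, classes resampled |
|---|---|---|---|---|---|
| 0.02 | 1.252 | 8.0% | 92.0% | 6.8% | 4.5% |
| 0.05 | 1.629 | 12.5% | 87.5% | 12.8% | 7.0% |
| 0.07 | 1.881 | 15.3% | 84.7% | not run | not run |
| 0.10 | 2.258 | 19.2% | 80.8% | 17.8% | 6.3% |
| 0.20 | 3.516 | 29.6% | 70.4% | 28.3% | 7.5% |

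With all 22 students per class, the path rate is 10.2% at ICC 0.02 and 27.0% at 0.10.

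**Baseline and time order.** The documents give no figure from which to size this bias, so it is argued by direction only. On timing, the programme takes about 5 to 8 weeks (Program). A T1 mediator would thus normally follow delivery and precede the T2 outcome.

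**The case against.** A reader might infer that the plan has chosen condition as the sole predictor, a student-level bootstrap, and no baseline adjustment or time order. The documents do not support that. Naming the exposure does not exclude covariates, no resampling unit is given, and no wave is ruled out. A class-level bootstrap, a multilevel mediation model, baseline covariates, or a T1 mediator with a T2 outcome would all fit the wording. This is also a journal article. Its full protocol and SAP are not shown, and such detail for a secondary mechanism analysis is often left to them.

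Further points stand against a stronger claim:

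- The mediator ICCs are assumed. At the planning value of 0.02 the simulated excess is small: 6.8% against 4.5%, with an error of 1 to 2 points.
- The T0 mediator may not exist. The HL-questionnaire serves as T0 (Data collection), and its described content (The classroom lessons) includes no climate or bullying items. Table 1, which might settle this, is not shown.
- Stratified randomisation by school is not plainly stated. The text speaks of equal distribution within each schoolyear and gives school effects as the reason.

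What remains is that the article does not merely defer the mediation analysis. It specifies exposure, mediators, outcome and interval method, and omits what it supplies for the neighbouring analyses. An analyst following it literally would produce the weak version.

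**Conclusion.** The point holds as a defect of specification: the mediation models, as written, permit a student-level, unadjusted, same-wave analysis of a class-randomised trial with a causal-chain hypothesis. It does not hold as a finding that such an analysis has been chosen, or that the intervals will in fact be too narrow.

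Under the literal implementation, the false-positive rate of the condition-to-mediator path would be about 8% at a mediator ICC of 0.02, 12.5% at 0.05 and 19% at 0.10, and the simulated indirect effect behaves similarly. These figures assume the ICCs, 13.2 students per class, and 0.17 as a coefficient of variation. The mediator-outcome path would in addition partly reflect pre-existing or reverse correlation, by an amount that cannot be computed here. The primary test and the primary conclusion are not affected.

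**What to change.** Add two or three sentences to the mediation paragraph:

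1. Obtain indirect-effect intervals by resampling whole classes within condition, or from a multilevel mediation model.
2. Adjust for the T0 outcome, which is already collected, and for the T0 mediator if the climate items are asked at T0.
3. Take the mediator at T1 and the outcome at T2, if the climate items are asked at T1. Label any same-wave analysis as supplementary.

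The cost is somewhat wider intervals and a little more code, with no new assessment wave. Limits remain. In the simulation, class resampling gave 4.5% to 7.5%, much closer to nominal than student resampling but not exact with 48 classes. Adjustment and time ordering reduce confounding of the mediator-outcome path without removing it, so conclusions about mechanism should stay cautious.

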**Methods:**

A cluster randomized controlled trial (RCT) with students randomized to HL or to care as usual will be conducted. Pre-vocational students in their first or second year (aged 12 to 14) will participate in the study. Subjects in both conditions will complete assessments at baseline and at 3- and 6-months follow-up. The primary outcome will be depressive symptoms using the Center for Epidemiologic Studies Depression Scale (CES-D) at 6-months follow-up. Secondary outcomes are well-being using the Warwick-Edinburgh Mental Well-Being Scale (WEMWBS) and life satisfaction (Cantril Ladder) measured at 6-months follow-up. Alongside the trial, an implementation study will be conducted to evaluate the implementation of HL, using both quantitative and qualitative methods (interviews, survey, and classroom observations).

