#### Statistical analyses

All statistical analyses will be conducted in R [48] by an independent researcher. Reporting of the results will be conducted in accordance with the (extended) CONSORT statement [23]. Analyses will be conducted based on the intention-to-treat (ITT) principle. The primary ITT analyses will be performed using linear mixed models, which adequately deal with missing at random data and can be used to account for the nested structure of the data; students nested within classes and repeated assessments nested within students [49]. Time, condition, and time by condition interactions will be specified as fixed effects to examine the effectiveness of the intervention on continuous primary and secondary outcomes. Baseline scores of the corresponding outcome will simultaneously be entered as fixed factors in the model to account for baseline imbalances. In accordance with the CONSORT statement [23], it will not be explicitly tested whether conditions statistically differ in their baseline characteristics. Hence, the decision whether models will be adjusted for additional covariates will not be based on whether statistical differences in these covariates exist at baseline. Instead, models will primarily be reported that are not adjusted for additional covariates. In an additional sensitivity analysis, it will be examined whether adjusting these models for the following baseline variables substantially changes conclusions drawn from the analyses: gender, age, immigration background, depressive symptoms, well-being, and life satisfaction. Post-hoc tests will be conducted to examine between-group differences at each timepoint using analyses of covariance (ANCOVA), including baseline scores as covariate. Based on estimated marginal means and corresponding standard errors from linear mixed models, between-group effect sizes at each timepoint will additionally be expressed as Cohen’s *d* with 95% confidence intervals.

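### The moderator models are listed without the main model's time terms and baseline score, so as written the tested interaction need not target the 6-month effect

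*Protocol article*

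**What the plan says.** The Protocol article, Statistical analyses, sets out the fixed effects of two families of linear mixed models.

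- **Main models.** "Time, condition, and time by condition interactions will be specified as fixed effects to examine the effectiveness of the intervention". It adds: "Baseline scores of the corresponding outcome will simultaneously be entered as fixed factors in the model". These mixed models are introduced as handling "students nested within classes and repeated assessments nested within students".
- **Moderator models.** The article states that "exploratory moderator analyses will be conducted to examine whether the effect of the intervention on primary and secondary outcomes depends on a priori defined variables". The moderators are "level of baseline CES-D depressive symptoms, gender, age, and immigration background". The models are "Separate linear mixed models with condition, the putative moderator, and the interaction of these two as fixed effects".

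The moderator sentence names no assessment, and it does not say that its terms are added to the main model. The time point of interest is stated in the abstract: "The primary outcome will be depressive symptoms using the Center for Epidemiologic Studies Depression Scale (CES-D) at 6-months follow-up". The abstract gives 6 months for well-being and life satisfaction too. The Discussion lists effect modification among the secondary aims, and Strengths and limitations says the moderator work will show for whom the program is effective.

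**The concern.** The article spells out fixed effects for both families, and the two lists differ. The moderator list has no time, no term linking time to condition, and no separate baseline score.

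If these models are fitted to repeated assessments, which is how the section introduces mixed models, a condition by moderator term without time is an average over whichever visits are in the data. It then answers whether the effect differs by moderator on average over follow-up. The trial's question is about 6 months.

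The two answers part when moderation changes between visits. That is plausible here, although the documents do not establish it. Individual consultations come after the final lesson, and extra sessions or referral for high scorers come later still. Differences by baseline CES-D could therefore be larger at T2 than at T1.

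At stake is the interpretation of the moderator results and whether they can be compared with the primary T2 effect. The primary analysis is not affected.

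**Working it through.** The plan states no figure for the moderator analysis, so there is none to reproduce.

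**Inputs from the Protocol article.** Assessments at T0, T1 (3 months) and T2 (6 months) (Design of the RCT). Baseline correlation r = 0.30, ICC 0.02 and n = 315 per condition (Sample size).

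**Assumptions not in the article.** Complete data; equal correlation 0.30 between all assessments; a balanced two-level moderator measured on students; for power only, a true difference in effect between moderator levels of 0.40 SD.

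**Step 1: what the listed term estimates.** Let D1 and D2 be the moderation at T1 and T2.

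- T2 only: D2.
- T1 and T2 together, no time term: (D1 + D2)/2.
  - Constant, D1 = D2: (D2 + D2)/2 = D2.
  - Present only at T2, D1 = 0: (0 + D2)/2 = 0.50 D2.
  - Fading, for example D1 = 0.40 and D2 = 0.20: (0.40 + 0.20)/2 = 0.30, which is 1.5 times D2.

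The average can therefore fall below, equal or exceed the 6-month value.

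**Step 2: cost of leaving out the baseline score.** Variance relative to an unadjusted single follow-up:

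- T2: 1.00 without adjustment; 1 − 0.30² = 0.91 with it, a reduction of 9%.
- Mean of T1 and T2: (1 + 0.30)/2 = 0.65 without; 0.65 − 0.09 = 0.56 with, a reduction of 0.09/0.65 = 14%.

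Because classes are randomised, the omission does not change what the interaction estimates. For baseline CES-D as moderator of CES-D, kept continuous, the baseline score is already in the model and nothing is lost.

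**Step 3: power at 315 per condition.** SE² = [4/(315/2)] × (1 − 0.02) × f = 0.0249 f, where f is the variance factor from step 2. Two-sided 5% test.

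| Model | f | SE | Power, 0.40 at T1 and T2 | Power, 0.40 at T2 only |
|---|---|---|---|---|
| T2, with baseline score | 0.91 | 0.150 | 76% | 76% |
| T2, no baseline score | 1.00 | 0.158 | 72% | 72% |
| T1+T2 pooled, no baseline score | 0.65 | 0.127 | 88% | 35% |
| T1+T2 pooled, with baseline score | 0.56 | 0.118 | 92% | 40% |

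In the last column the pooled models have an expected coefficient of 0.20.

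**Step 4: simulation check.** Forty simulated trials per scenario with a true value of 0.40 gave these mean estimates (absolute value):

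- Constant moderation: pooled T1+T2 0.40; T2 with baseline 0.40; T2 contrast from the model with time by condition by moderator 0.41.
- Moderation at T2 only: 0.17, 0.38 and 0.38.

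These agree with step 1 within simulation error.

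**The case against.** The strongest reply is that the sentence may already describe a T2 model. It refers to effects on the primary and secondary outcomes, and the abstract places these at 6 months. With T2 as the only outcome row, a mixed model is still needed for students within classes, a time term could not be estimated, and the listed interaction is exactly 6-month moderation. This stands, and it is why the point cannot be put as an outright error. It does not settle the matter. For comparisons at a single time point the same section names ANCOVA, it introduces mixed models for repeated assessments, and it ties the mediation outcomes to follow-up but gives the moderator models no assessment.

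Second, pooling T1 and T2 need not weaken anything. With constant moderation the pooled term is unbiased for the T2 value and has more power (88% against 76%). This also stands: attenuation depends on how moderation changes over time.

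Third, the analyses are exploratory, and an article may condense them. This limits the weight of the point. But the article does state a list of terms, and that list departs from the main model, so this is more than a detail left for later.

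A reader might also infer that the interaction is diluted because T0, where no moderation can exist, is averaged in. With T0 rows it would be (0 + D1 + D2)/3, or 0.67 of the 6-month value under constant moderation. Nothing in the article makes T0 an outcome row in these models, and the main model uses baseline as a covariate, so that reading is not supported.

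**Conclusion.** The point holds in a limited form. The listed moderator terms omit the main model's time terms and baseline score, so the tested interaction need not be moderation of the 6-month effect. If T1 and T2 are fitted together, it equals the T2 value under constant moderation and half of it if moderation arises only at T2. The second cost is efficiency: at r = 0.30, baseline adjustment would remove about 9% of the variance at T2 (76% against 72% power in the example), except where baseline CES-D moderates CES-D.

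The 9% rests on the plan's correlation for the primary outcome; none is given for the secondary outcomes. The power figures rest on the assumed 0.40 SD, the balanced moderator and equal correlations, and are illustrations only.

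The documents do not support saying that the term definitely misses the 6-month effect, that it is always attenuated, or that leaving out the baseline score biases it. The change is worth making because the moderators are declared in advance, and the quantity tested should be fixed in advance too.

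**What to change.** Define the moderator models as extensions of the main model, with the baseline score of the corresponding outcome included, in one of two ways:

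1. T2 as the outcome, with condition, moderator, their interaction and a class random effect; or
2. T1 and T2 as outcomes, with time, condition by time by moderator and all lower-order terms, and random effects for class and student, reporting the condition by moderator contrast at T2.

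Keep baseline CES-D continuous, so that for the CES-D outcome it serves as both covariate and moderator.

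The cost is a change of wording; no data or visits are added and the analyses stay exploratory. The one downside is precision. If moderation is constant over time, the T2 contrast has a larger standard error than a pooled T1+T2 term (0.150 against 0.118, both baseline-adjusted, under the assumptions above). If the average over follow-up is also of interest, report it separately and label it as such.
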